**Figure 2 figure2:**
[figure not shown]
An overview of the research project, including study designs, data sources, included participants, and time periods.

### Estimated Sample Size and Power

#### Sample Size Calculation

Calculation of the sample size was initially based on objective 1, using Minitab 16. The calculation was based on data from the SPR 2017 with a 7% initial prevalence of mental ill-health among pregnant women in the Västmanland Region [37], with an expected increase to 10% due to the rise in detection attributable to the program’s implementation. In order to detect an increase by 3 percentage points in identified mental ill-health, with 80% power and a significance level of 5% (2-sided test), at least 534 pregnant women had to be included in each group. The inclusion of several different maternity clinics in the project was also taken into consideration, and we estimated a dropout rate of approximately 20%. This meant that 640 pregnant women had to be included in each group for both pre- and postimplementation measurements.

However, the emergence of the COVID-19 pandemic introduced unforeseen challenges, particularly with regard to participant recruitment and data representativeness. It was hypothesized that the pandemic may have influenced the prevalence of mental ill-health in the target population, potentially confounding the original pre-post comparisons.

In response, a revised strategy for objective 1 was implemented. A new ethical approval was obtained to extend data inclusion and allow for the anonymous use of aggregated register data from the SPR, covering all pregnant women in the Västmanland Region during 2017-2019 (preimplementation) and 2021-2023 (postimplementation). This adjustment enabled a substantial increase in sample size and improved the generalizability of findings for objective 1 while minimizing selection bias and increasing statistical power.

Importantly, although the revised strategy for objective 1 now relies on registry-based data with a broader population base, the original sample size calculations remain valid for objectives 2-4, which continue to use the survey-based data set from pre- and postimplementation phases. The sample size for these objectives was not altered, and the statistical power for each is described in general terms in the following paragraphs.

Furthermore, addressing the recruitment challenges faced for objectives 2-4, it is crucial to note the difficulties encountered in achieving the initial target sample size. Specifically, we aimed to recruit 640 participants in the pre-implementation phase but were only able to enroll 487. This shortfall contrasted with the implementation phase, during which we successfully recruited 942 participants.

Given the research design outlined in the preceding paragraphs, together with the collected data, this will provide the opportunity to test a wide array of hypotheses in the current research area. Specifically, it is suitable for testing hypotheses involving both dichotomous outcomes, with lower or higher pre-implementation prevalence, and a wide range of continuous outcomes, including when testing for small, standardized differences.

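### 534 women per group gives about 42% power for 7% versus 10%, not 80%, yet the calculation is declared still valid for Objectives 2-4

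*Protocol article*

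**What the plan says.** The section Sample Size Calculation takes as baseline a "7% initial prevalence of mental ill-health among pregnant women in the Västmanland Region", from 2017 register data, "with an expected increase to 10% due to the rise in detection attributable to the program’s implementation". For that 3-point rise it concludes that "with 80% power and a significance level of 5% (2-sided test), at least 534 pregnant women had to be included in each group". It then mentions the number of clinics and a dropout of about 20%, and continues: "This meant that 640 pregnant women had to be included in each group".

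Objective 1 was later moved to register data. Of the survey-based cohort the same section says that "the original sample size calculations remain valid for objectives 2-4" and that the sample size for these objectives was left unchanged. It then reports the shortfall: "we aimed to recruit 640 participants in the pre-implementation phase but were only able to enroll 487". The post-implementation group reached 942.

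The next section, Dichotomous Outcomes, gives detectable differences for this cohort at 80% power: 5 points at 10% prevalence and 4 points at 5% prevalence. The Statistical Power sections of Objectives 3 and 4 repeat a detectable change of about 4 to 5 points. Objective 2 has its own power statement, based on 142 events and a hazard ratio of about 1.65.

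**The concern.** Every input needed to check the sample size is printed, and 534 is far too small for them. A 3-point difference near a prevalence of 8.5% needs well over a thousand women per group.

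The error matters because the article still relies on it. This calculation set the recruitment target for the cohort that serves Objectives 2-4, including the primary Objective 2, and the article endorses it as valid for them. A reader who accepts that sentence will believe the cohort was sized for a 3-point change with 80% power, and may take a null result as evidence that no such change occurred.

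**Working it through.** **Inputs** (Sample Size Calculation): p1 = 0.07, p2 = 0.10, difference 0.03, two-sided α = 0.05 (z = 1.96), power 80% (z = 0.8416), equal groups, dropout about 20%. Enrolled: 487 and 942.

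**1. Attempt to reproduce 534.** With the pooled-variance formula and mean proportion 0.085:

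n = [1.96·√(2 × 0.085 × 0.915) + 0.8416·√(0.07 × 0.93 + 0.10 × 0.90)]² / 0.03²

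n = (0.7730 + 0.3315)² / 0.0009 = 1,355.4, so 1,356 per group.

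Other two-sample versions do not reach 534 either:

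| Method | n per group |
|---|---|
| Two-sided, pooled variance | 1,356 |
| Two-sided, unpooled variance | 1,353 |
| Two-sided, arcsine | 1,346 |
| Two-sided, continuity-corrected | 1,422 |
| One-sided, pooled variance | 1,068 |
| One-sided, continuity-corrected | 1,134 |

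The stated figure is too small by a factor of about 2.5 (1,356/534). The article does not show how it arose. Two coincidences can be noted but not confirmed: 534 is half of the one-sided 1,068, and it is close to what 7% versus 12% would need (536 unpooled, 539 pooled).

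**2. Power for 7% versus 10%**, as Φ[(0.03 − 1.96·s0)/s1], where s0 is the standard error under the null (pooled) and s1 under the alternative:

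| Group sizes | s0 | s1 | Power |
|---|---|---|---|
| 534 / 534 | 0.01707 | 0.01704 | 42.0% |
| 640 / 640, no dropout | 0.01559 | 0.01557 | 48.6% |
| 487 / 942, as enrolled | 0.01595 | 0.01514 | 46.7% |

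**3. Rise from 7% detectable with 80% power.** With 534 per group it is about 5.0 points. With 487 and 942 it is about 4.6 points.

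**4. Comparison with the article's own figures.** At 487 and 942 the same method gives 5.2 points from a 10% baseline and 4.1 points from 5%. This agrees with the 5 and 4 points under Dichotomous Outcomes. The enrolled cohort of 1,429 women therefore cannot, on the article's own figures, detect the 3 points that 1,068 women (2 × 534) are said to detect.

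**5. Dropout.** 534 × 1.2 = 640.8, which matches 640. But 640 × 0.8 = 512, below the stated minimum of 534. The correct inflation is 534/0.8 = 667.5, so 668. Applied to the correct sample size it is 1,356/0.8 = 1,695 per group.

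**The case against.** The strongest reply accepts the arithmetic and disputes the consequence.

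- **Separate power statements exist.** Dichotomous Outcomes and the power sections of Objectives 2, 3 and 4 give their own figures, and none claims sensitivity to 3 points. The shortfall to 487 is reported openly. A careful reader of a null result would use those figures. This stands, and it limits the practical harm.
- **The 7% versus 10% contrast was the original Objective 1 endpoint.** Objective 2 is a Cox analysis, Objective 3 compares referral proportions, and Objective 4 uses ratings and yes/no items. The 47% is therefore not the power of those analyses. This also stands. It equally undercuts the article's statement that the original calculation carries over to them.
- **No decision now depends on 534 or 640.** Objective 1 has a separate calculation on 8,246 and 7,611 births, and recruitment for the other objectives is closed. This is true, and it is why the remedy is only to the text.
- **The dropout slip is small.** 640 against 668 is a gap of about 4%. It is secondary to the main error.

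None of this makes 534 correct, and the validity sentence still conflicts with the detectable differences given elsewhere in the article.

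**Conclusion.** The concern holds. On the article's own inputs the requirement is about 1,356 per group, not 534, and power at 534 per group is about 42%, not 80%. At the enrolled 487 and 942 it is about 47%, with a detectable rise of about 4.6 points from 7%. The statement that the calculation remains valid for Objectives 2-4 is wrong on two counts: the calculation never supported its stated effect, and the pre-implementation group fell below even 534.

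These figures assume a two-sample normal-approximation test on independent women, without clustering by clinic or covariate adjustment, and outcomes for everyone enrolled. Positive correlation within clinics would normally raise the required number. Objective 1 in its register-based form does not rest on this figure. The risk of over-reading null results in Objectives 2-4 is real but tempered by the separate power statements for each objective.

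**What to change.** In Sample Size Calculation:

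1. Replace 534 and 640 with about 1,356 and, at 20% dropout, 1,695 per group. If the historical target is to stay on record, state that 534 per group supports a rise of about 5 points from 7%, and that allowing for 20% dropout would have required 668.
2. Delete the sentence that the original calculations remain valid for Objectives 2-4, and refer instead to the detectable differences already given for each objective.
3. State that with 487 and 942 women the power for 7% versus 10% is about 47%, and that the smallest rise from 7% detectable with 80% power is about 4.6 points.

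The cost is a text correction. Recruitment is complete, and neither the enrolment nor the planned analyses need to change.

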#### Dichotomous Outcomes

The minimum detectable difference (MDD) with this design varies inversely with the pre-implementation prevalence. For instance, it can reliably, with 80% power, discern an 8% change in a 50% pre-implementation prevalence and more refined changes—such as 5% at a 10% prevalence or 4% at a 5% prevalence, with the same power at a higher prevalence (90% and 95%). This makes the design ideal for testing hypotheses expected to result in either a marked increase or decrease in prevalence rates, ensuring accurate detection of both common and rare conditions, as well as self-rated dichotomous factors according to the questionnaire data.

#### Continuous Outcomes

The study has the capacity to detect minimal standardized differences as small as 0.15 with 80% power. This level of sensitivity is particularly beneficial for hypotheses investigating subtle changes in continuous measures, such as gradual improvements or declines in health measures, psychological scores, continuous variables according to the questionnaire data, or any other continuous outcomes that fall well within the scope of this design. Given these conditions, the study design is suitable for a broad spectrum of hypotheses and can be used effectively to advance our knowledge in this field.

#### Handling of Missing Data

The proportion of missing data is expected to be low. Based on register quality and the data collection design, fewer than 5% of individuals are anticipated to have missing values for any variable included in the planned analyses. To assess whether the assumption of missing completely at random (MCAR) is valid, an MCAR test will be performed. This test examines whether the probability of missingness is independent of both observed and unobserved variables. If the assumption of MCAR is supported, complete-case analysis will be deemed appropriate. Should the test indicate that data are not MCAR, we will explore the pattern and mechanism of missingness further, applying multiple imputation or models to assess the robustness of results under plausible missing data scenarios. The final manuscripts will report the MCAR test results, the chosen method, and any observed differences in findings.

### Objective 1

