#### Participants and Data Collection

Pregnant women who could communicate in Swedish and who were enrolled in early pregnancy at maternity clinics in the Västmanland Region were invited to participate in the study. In the poststudy, patients from all 25 maternity clinics in the region were invited to participate. The women were sent an envelope by post with an invitation to participate, a consent form, and a questionnaire. Consent covered the review of medical records (objectives 2 and 3) and questionnaire data (objective 4).

Participant inclusion was completed in 2022. Pre-implementation (2019), a request for participation was sent to 887 patients, and 487 were included. Questionnaire 2 was sent to 512 patients, and 314 responded to both questionnaires 1 and 2. Postimplementation (2020-2021), a request for participation was sent to 2368 patients, and 942 were included. Questionnaire 2 was sent to 837 patients, and 708 responded to both questionnaires 1 and 2.

A review of medical records will be conducted in the specific data system for antenatal and perinatal health care used in the region, to extract data for objective 2.

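### Objective 4: the under-5% missing-data expectation conflicts with the questionnaire counts already in hand, and an MCAR test alone may admit complete-case analysis

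*Protocol article*

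**What the plan says.** The section Handling of Missing Data stands ahead of the individual objectives and exempts none of them. It expects that "fewer than 5% of individuals are anticipated to have missing values for any variable included in the planned analyses", a figure it rests on two grounds: "Based on register quality and the data collection design". It then plans an MCAR test and describes it thus: "This test examines whether the probability of missingness is independent of both observed and unobserved variables". The decision rule is: "If the assumption of MCAR is supported, complete-case analysis will be deemed appropriate". Only if the test points away from MCAR does the plan explore the mechanism further, "applying multiple imputation or models to assess the robustness of results under plausible missing data scenarios". The manuscripts are to report the test result, the method chosen and any differences in findings.

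The section Objective 2, Participants and Data Collection, to which Objective 4 refers for its participants, gives observed counts. Pre-implementation, "a request for participation was sent to 887 patients, and 487 were included", and "Questionnaire 2 was sent to 512 patients, and 314 responded to both questionnaires 1 and 2". Post-implementation, 2368 women were invited and 942 included, and "Questionnaire 2 was sent to 837 patients, and 708 responded to both questionnaires 1 and 2". Objective 4 draws its outcomes from these questionnaires, the second of which was administered after gestational week 33. Data collection for Objective 4 ended in 2022.

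**The concern.** The 5% figure is more than a forecast for Objective 4, because the data it describes had already been collected when the article was written. The counts in the same article are several times larger and differ between the two periods.

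The rule built on that figure has two faults of its own. First, a test of MCAR works from observed values, so it cannot show whether missingness depends on values nobody recorded. Second, MCAR is the null hypothesis of such a test. The assumption can be called supported only in the sense that it was not rejected, and that does not establish it.

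Objective 4 compares self-rated mental health and help received. Women with worse mental health may be less likely to return a late-pregnancy questionnaire. If so, and if the loss or its selectivity differs by period, the pre-post contrast is distorted, and the stated rule could still approve the complete-case result without any check on it.

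**Working it through.** **Inputs** (Objective 2, Participants and Data Collection):

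| | Included | Sent questionnaire 2 | Answered both |
|---|---|---|---|
| Pre | 487 | 512 | 314 |
| Post | 942 | 837 | 708 |

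**Step 1. Loss among women included** = 1 − (answered both ÷ included).
- Pre: (487 − 314)/487 = 173/487 = 35.5%
- Post: (942 − 708)/942 = 234/942 = 24.8%
- Overall: 407/1429 = 28.5%

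**Step 2. Loss among women sent questionnaire 2** = 1 − (answered both ÷ sent).
- Pre: (512 − 314)/512 = 198/512 = 38.7%
- Post: (837 − 708)/837 = 129/837 = 15.4%

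The stated figure of under 5% is not reproduced with either denominator. The gap between periods is 35.5 − 24.8 = 10.7 points on women included and 38.7 − 15.4 = 23.3 points on questionnaires sent.

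**Step 3. Consistency of the counts.** Pre-implementation, 512 − 487 = 25 more women were sent questionnaire 2 than were included, without explanation. Post-implementation, at least 942 − 837 = 105 included women (11.1%) were not sent it, so the loss passes 5% there before any non-response.

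**Step 4. What a complete-case comparison could cost.** Suppose non-responders score g SD worse than responders. Complete cases then overstate a period's mean by (missing share × g). The net error in the pre-minus-post difference is

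B = 0.355 × g(pre) − 0.248 × g(post).

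The documents give no values for g, so those below are assumptions.

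| g(pre) | g(post) | B |
|---|---|---|
| 0.5 | 0.5 | 0.178 − 0.124 = +0.05 SD |
| 0.5 | 0.2 | 0.178 − 0.050 = +0.13 SD |
| 0.2 | 0.5 | 0.071 − 0.124 = −0.05 SD |

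On scales where higher is better, a positive B understates an improvement after implementation and a negative B overstates it.

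**Step 5. Precision.** Detectable standardized difference = (1.96 + 0.84) × √(1/n₁ + 1/n₂), 2-sided 5%, 80% power.
- With 487 and 942: 0.156, which matches the stated value of about 0.15.
- With 314 and 708: 0.190. Power at 0.15 falls from 77% to 60%.

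The Objective 4 power statement therefore corresponds to everyone included, not to women with both questionnaires.

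**The case against.** The strongest reply is about scope, and it stands. Both primary objectives and Objective 3 use register or medical-record data, which do not depend on questionnaire 2; under 5% may be reasonable there. Objective 4 is secondary, and its Measures section does not say which items come from which questionnaire. Questionnaire 1 was posted with the invitation and consent form, so items taken only from it may be nearly complete. A reader might infer that missing data undermine the whole plan; the documents do not support that.

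Second, the counts are of women who answered both questionnaires. A reader might take 35.5% and 24.8% as the exact questionnaire 2 loss. That would require every included woman to have answered questionnaire 1 and, pre-implementation, a mailing list consistent with the number included. Some of the 105 post-implementation women may not have been sent it for legitimate reasons that the article does not give. This limits the exactness of the figures but does not bring them under 5%.

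Third, the test may not be weak against attrition related to measured baseline scores. Comparing questionnaire 1 mental health between 1022 women with both questionnaires and 407 without has about 93% power for a 0.2 SD gap and 99% for 0.25 SD (normal approximation, assuming that score is observed in all of them; a test with several degrees of freedom has less). Rejection would bring in the imputation or robustness models already planned, so it would be wrong to say the plan lacks them. What remains is dependence on unobserved values. The test cannot see it, and multiple imputation under missing at random does not cure it either, which is why a sensitivity analysis is needed.

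**Conclusion.** The point holds for Objective 4 outcomes that use questionnaire 2. The under-5% statement is contradicted by the article's own counts, the description of the MCAR test is wrong, and non-rejection is not a sound sole ground for complete-case analysis. These are faults in what the article states, not details left to an analysis plan.

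The missing shares come straight from the counts, subject to the unreconciled pre denominator. The bias does not: its size and direction are unknown, and −0.05 to +0.13 SD only illustrates assumed gaps of 0.2 to 0.5 SD. A reader might infer that the Objective 4 result is biased by nearly the whole 0.15 SD the study claims to detect. That needs a gap 2.5 times larger pre than post, which nothing in the documents supports; reversing the gaps changes the sign.

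This should be fixed, but it concerns a secondary objective and does not touch the primary ones.

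**What to change.** 1. Limit the under-5% expectation to register and medical-record data.
2. Report questionnaire losses by period, with the denominator named, and reconcile 512 sent with 487 included. Say why questionnaire 2 went to fewer women than were included post-implementation.
3. Correct the MCAR sentence: the test examines observed data only, and non-rejection does not establish MCAR.
4. Remove the test as the gate for Objective 4. For questionnaire 2 outcomes, use multiple imputation with questionnaire 1 and medical-record predictors, plus a missing-not-at-random (delta-shift) sensitivity analysis, whatever the test shows. Present complete cases as secondary.
5. State which items come from which questionnaire. Treat conditional items (help from extra visits, time to contact with another provider) as not applicable, rather than missing, where the condition is not met; they should not be imputed for those women.

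The cost is revised wording and modest extra analysis on data already held.

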#### Study Design

The study design incorporates pre- and poststudy measurements with comparison of pre- and postimplementation of a program for psychosocial assessment.

#### Participants and Data Collection

Data will be extracted from the SPR for all registered pregnant individuals in the Västmanland Region, preimplementation (2017-2019) and postimplementation (2021-2023) of the program. We chose 3-year periods for data extraction in order to obtain more representative data concerning any changes, as well as to counteract the effects of the COVID-19 pandemic.

The SPR is a national quality register with certification level 1 (the highest level). This accessibility is a prerequisite for the development of health care and consequently, for improving the health of pregnant women and their children, as well as promoting equitable care and high quality in the chain of care. Improvement work is facilitated by rapid feedback of SPR data and results. The SPR is a rich source for research in the field of pregnancy and childbirth. Of the 99,011 births registered in Sweden in 2023, 97,964 were registered in the SPR, a coverage rate of 98.9% [7].

#### Measurements

Objective 1 includes data from the SPR, which will be compared pre- and postimplementation of the program for psychosocial assessment, and captures the prevalence of patients who have received (1) medical treatment prepregnancy or during pregnancy, (2) psychological treatment for mental ill-health prepregnancy or during pregnancy, and (3) both medical and psychological treatment prepregnancy or during pregnancy.

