#### Primary Objectives

##### Objective 1

The first objective aims to answer: Does a program for psychosocial assessment during pregnancy influence the prevalence of pregnant women receiving psychological or medical treatment for mental ill-health?

##### Objective 2

The second objective aims to answer: Does a program for psychosocial assessment during pregnancy influence the time point for identification of mental ill-health in pregnant women?

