**Figure 1 figure1:**
[figure not shown]
Overview of the program for psychosocial assessment (Västmanland Region), including maternity clinic visits and questions about mental health and social factors at various gestational weeks (+days); the visits after the dashed line (postpartum) will not be included in this evaluation. EPDS: Edinburgh Postnatal Depression Scale; GAD-2: Generalized Anxiety Disorder 2-item.

At the first visit (gestational weeks 5-7), the midwife asks all women questions about prior and ongoing serious mental illness or perinatal mental illness and treatment, as well as family history of serious mental illness or perinatal mental illness. At the second visit, which takes place a few weeks later (gestational weeks 8-12), questions are asked concerning prior and ongoing less serious mental ill-health, symptoms of stress and anxiety, social situation, support from relatives and network, and experiences with domestic violence.

Moreover, to specifically identify symptoms of depression and anxiety during the conversation about mental ill-health, the midwife asks all women the Whooley questions [30] and GAD-2 questions [31].

The Whooley questions are designed to identify symptoms that may be present in depression. The questions are as follows:

During the past month, have you often been bothered by feeling down, depressed, or hopeless?During the past month, have you often been bothered by little interest or pleasure in doing things?

The GAD-2 is a brief initial screening tool aimed at identifying symptoms of anxiety. The questions are as follows:

Over the last two weeks, how often have you been bothered by feeling nervous, anxious, or on edge?Over the last two weeks, how often have you been bothered by not being able to stop or control worrying?

If the woman responds in the affirmative to any of these 4 questions, the Edinburgh Postnatal Depression Scale (EPDS) [32] is administered to aid further assessment [2,21,24]. The EPDS is a comprehensive 10-item self-rated scale for identifying symptoms of depression [32]. It has been validated in Sweden for use during pregnancy [33].

The Fear of Birth Scale [34,35] is a self-rated scale administered at gestational week 24 to identify fear of birth. If needed, additional visits are offered for childbirth preparation. There is also the possibility of referral to the Obstetrics Department’s specialist unit for assessment and care planning with a midwife, obstetrician, and perinatal psychologist.

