#### Statistical Analysis

Logistic regression analysis, including an indicator variable for pre- and postimplementation, will be performed. The model will also include variables to adjust for potential confounding variables (eg, age, primiparous women, civil status, employment status, maternity clinic), selected according to the disjunctive cause criterion [38].

The effect measure will be the odds ratio (OR) with 95% CIs.

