#### Measures

Objective 3 includes data extraction from medical records for the following variables: whether the patient received psychological or medical treatment for mental ill-health that was initiated prepregnancy, whether the patient received psychological or medical treatment for mental ill-health that was initiated during pregnancy, and referral pathways to other health care providers when mental ill-health is identified.

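### The Objective 1 measures count treatment received only before pregnancy, which the programme cannot change, so the odds ratio is pulled toward 1 and is open to drift in prior treatment or its recording

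*Protocol article*

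**What the plan says.** All of this is in the protocol article.

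- **Question.** Objective 1, one of two primary objectives, asks whether the programme will "influence the prevalence of pregnant women receiving psychological or medical treatment for mental ill-health".
- **Measures.** Objective 1, Measurements, gives three: "medical treatment prepregnancy or during pregnancy, (2) psychological treatment for mental ill-health prepregnancy or during pregnancy", and third "both medical and psychological treatment prepregnancy or during pregnancy". All three use the same window.
- **First contact.** Under Description of the Program for Psychosocial Assessment: "At the first visit (gestational weeks 5-7), the midwife asks all women questions about prior and ongoing serious mental illness". The same sentence goes on to cover treatment.
- **Analysis.** Objective 1, Statistical Analysis: "Logistic regression analysis, including an indicator variable for pre- and postimplementation, will be performed". The periods are 2017-2019 and 2021-2023. No comparison region or time trend is stated, and prior treatment is not among the example covariates.
- **Contrast.** Objective 3, Measures, keeps the two windows apart, with one variable for "psychological or medical treatment for mental ill-health that was initiated prepregnancy" and another for "psychological or medical treatment for mental ill-health that was initiated during pregnancy".

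**The concern.** The measure and the question cover different things. A woman whose treatment ended before she conceived is an outcome event in either period, whatever the programme does. This has three consequences.

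1. **Dilution.** Such women add events that the programme cannot move. A woman who had psychological treatment earlier and resumes it because of the programme is already counted under psychological treatment, so that measure cannot register her. The Introduction says that women with moderate-to-severe illness before pregnancy are at increased risk of relapse and should be found early, so the measure is insensitive in a group that the programme targets.
2. **Drift.** The effect is the coefficient of a before/after indicator. Any change across these years in how many women were treated before pregnancy goes straight into it.
3. **Recording.** The programme has midwives ask every woman about past illness and treatment in a structured way. Recorded prior treatment could therefore rise without any additional treatment being given.

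At stake is what a primary odds ratio above or near 1 would mean.

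**Working it through.** **Inputs from the article.** n1 = 8246 and n2 = 7611, baseline 7%, two-sided 5% test (Objective 1, Statistical Power); expected rise from 7% to 10%, a factor of 10/7 (Sample Size Calculation).

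**Assumptions, not in the article.** The 7% measures the Objective 1 composite. A share q of it is treatment before pregnancy only. The programme multiplies the remainder by 10/7 and leaves the prepregnancy-only part unchanged.

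**Formula.** For proportions p1 and p2, with pooled proportion p:

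- SE0 = √[p(1−p)(1/n1 + 1/n2)]
- SE1 = √[p1(1−p1)/n1 + p2(1−p2)/n2]
- power = Φ[(|p2−p1| − 1.96·SE0)/SE1]
- OR = [p2/(1−p2)] / [p1/(1−p1)]

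**The plan's own figure.** The article gives a minimum detectable difference of 0.8 points at 80% power. This does not reproduce: power at 7.0% against 7.8% is 49%, and 80% power needs an increase of 1.18 points. That is a separate matter and nothing below rests on the 0.8.

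**Dilution, worked for q = 50%.** The 7% splits into 3.5% and 3.5%. The during-pregnancy part becomes 3.5% × 10/7 = 5.0%, so the composite becomes 3.5% + 5.0% = 8.5%.

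- Composite, 7.0% against 8.5%: OR = (0.085/0.915)/(0.07/0.93) = 1.23. SE0 = 0.00424 and SE1 = 0.00426, so (0.015 − 0.00832)/0.00426 = 1.57 and power is 94%.
- During pregnancy only, 3.5% against 5.0%: OR = (0.05/0.95)/(0.035/0.965) = 1.45. SE0 = 0.00320 and SE1 = 0.00322, so (0.015 − 0.00626)/0.00322 = 2.72 and power is 99.7%.

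The same steps at other shares:

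| q | Composite | OR | Power | During pregnancy | OR | Power |
|---|---|---|---|---|---|---|
| 0 | 7.0% to 10.0% | 1.48 | >99% | 7.0% to 10.0% | 1.48 | >99% |
| 25% | 7.0% to 9.25% | 1.35 | >99% | 5.25% to 7.5% | 1.46 | >99% |
| 50% | 7.0% to 8.5% | 1.23 | 94% | 3.5% to 5.0% | 1.45 | 99.7% |
| 75% | 7.0% to 7.75% | 1.12 | 44% | 1.75% to 2.5% | 1.44 | 91% |
| 90% | 7.0% to 7.3% | 1.05 | 11% | 0.7% to 1.0% | 1.43 | 54% |

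**Drift with no programme effect.** Let only prepregnancy-only treatment, or its recording, rise, so that p2 = 7% + d.

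| d (points) | OR | Chance of a significant result |
|---|---|---|
| 0.5 | 1.08 | 23% |
| 1.0 | 1.16 | 67% |
| 1.5 | 1.23 | 94% |

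A drift of 1.5 points gives the same composite odds ratio, 1.23, as a real programme effect at q = 50%. The composite cannot tell them apart.

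**The case against.** **The wording may be shorthand.** The Measurements sentence could condense register fields that will be reported separately, and a journal article does not show the register's structure. That is possible, but the article does not say so, and under Objective 3 it separates the two windows explicitly. If the fields are separate, one sentence settles the matter.

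**The size is assumed.** This stands. The share q is not given, and the article calls the 7% a prevalence of mental ill-health or of identified cases, never the treatment composite. At shares of 25% or less both outcomes have over 99% power under these assumptions. A reader might infer from the 49% power at +0.8 points that the composite leaves Objective 1 underpowered. It does not show that: holding an absolute difference fixed and varying the baseline mainly shows variance rising with prevalence, and 0.8 points is not the anticipated effect.

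**Questions were already being asked.** This stands too. A reader might infer that asking about mental health was new. The section on Swedish guidelines says that the 2016 guidance already recommended asking each woman in early pregnancy, without stipulating structured identification. Fuller recording is therefore a possibility, not a stated fact.

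**Any before/after comparison absorbs drift.** True. The article concedes pandemic confounding and says the analysis will need to account for it. It does not mention the route through prepregnancy treatment, which is the part that the outcome definition can remove.

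**Objective 3 already has the split.** It does, but as a secondary objective in 487 and 942 consenting women, not in the whole register population.

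**Conclusion.** The concern holds as a mismatch between a primary question and its measures. Nothing in the article reconciles them. Followed as written, the plan puts any change in prepregnancy-only treatment, or in its recording, into the primary odds ratio.

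The direction of the dilution is clear, but its size is conditional on the unknown share: negligible for power at 25%, modest at 50% and serious at 75% or more. The drift result does not depend on that share. It depends on how large the drift was, which the documents do not show, and on the 7% being the composite's baseline. The documents do not support saying that drift or a recording change has occurred, only that this outcome could not distinguish either from a programme effect.

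**What to change.** Before extraction, which is planned for 2025-2026:

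1. Define the primary Objective 1 outcome as psychological and/or medical treatment received during pregnancy, including treatment continued from before pregnancy. Restricting it to treatment started in pregnancy would be narrower than the stated question, which is about receiving treatment.
2. Report prepregnancy-only treatment separately, using the same model, as a check on drift and recording change. Call the check imperfect: the programme may itself alter recording, so a rise could not be assigned to one cause.
3. If the register cannot separate the timing, say so, limit the Objective 1 conclusion accordingly, and point to the Objective 3 record data for the during-pregnancy comparison.

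The cost is a change of outcome wording and one additional reported outcome. The split depends on the register recording timing separately, and it does not remove secular change in during-pregnancy treatment itself.
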